### Measures

The participants will be invited to complete a sociodemographic questionnaire. The clinical characteristics will be extracted from the participant’s medical records, including the risk factors, cardiac history, results of cardiac examinations, comorbidities, and medications in use.

#### Primary Outcome: Compliance of Cardiac Rehabilitation Sessions

The primary outcome of this trial was carefully chosen. A correct exercise compliance promotes positive changes in behavior and lifestyle [18], besides reducing the risk for rehospitalization and improving quality of life [26].

The compliance on CR sessions will be analyzed by the percentage of participants who completed at least 75% (45/60) of the sessions. This parameter will be evaluated after 3 months.

#### Secondary Outcomes: Functional Capacity, Cost, Morbidity, Control of Risk Factors, Heart Health Behaviors, and Usability

Changes in the functional capacity will be analyzed using the incremental shuttle walk test (ISWT), a walking test that evaluates the functional capacity through the analysis of the walked distance [27].

The cost analysis and morbidity variables will be evaluated after 3 months and after 3 and 6 months, respectively, in both groups. The analysis of the programs’ cost will be made by calculating the total sum of each procedure in the 2 groups, considering the hospital’s payments table for procedures and services. Morbidity will be evaluated through a survey to identify the number of hospitalizations, complications, and the presence of adverse clinical events during the study period.

Resting blood pressure, measured in mm Hg, and waist circumference, measured in cm, will be analyzed. Waist circumference will be assessed at the superior border of the iliac crest, in accordance with the standardized guideline [28]. Alterations in fasting glucose (mg/dL), glycohemoglobin (%), and total cholesterol (mg/dL) values will be analyzed before the CR program and reanalyzed after 3 and 6 months.

Other behaviors will be assessed using psychometrically validated scales. Quality of life will be assessed using the Short Form 36 questionnaire [29], depression by the Patient Health Questionnaire-9 [30], the physical activity level using the Duke Activity Status Index Score [31], and the level of knowledge by the Coronary Artery Disease Education Questionnaire-Short Version [32].

Alterations in fasting glucose, glycohemoglobin, total cholesterol values, measures of resting blood pressure, waist circumference, quality of life, depression, physical activity level, functional capacity, and knowledge about coronary diseases will be evaluated at the beginning and after 3 and 6 months of the intervention in both groups. The assessment schedule is reported in Table 1.

The usability of the equipment used in the home-based group will be verified through the System Usability Scale after 3 months [33].

**Table 1 table1:** Schedule of outcome assessments for control and home-based groups.

Outcome measures			Control group			Home-based group		
			Baseline	3 months	6 months	Baseline	3 months	6 months

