**Conclusions:**

This is the first study in Brazil comparing the traditional cardiac rehabilitation approach with a novel, home-based protocol that uses an accessible and low-cost technology. If positive results are obtained, the study will contribute to establish a new and viable model of cardiac rehabilitation.

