#### Home-Based Cardiac Rehabilitation

The participants of this program will perform their exercise mostly at home. Weekly phone calls will be programmed to check the correct execution of the previous stage of the program and also identify and register the presence of symptoms and undesirable effects. Monthly meetings will be programmed for educational activities to verify if the exercises and training diary are being both performed and compiled correctly and to address any kind of issue by the participants.

This intervention will have a duration of 12 weeks, with a total of 60 sessions: 2 supervised sessions and 58 home sessions (5 exercise sessions per week).

During the first week, all individuals of the home-based group will be receiving training regarding the utilization of the monitoring equipment. A heart rate monitor with the heart rate zone individually calculated will be given to each participant at the first supervised session. Furthermore, all participants of this group will be using a step counter (pedometer) to monitor the number of prescribed exercises as well as an aid to compile the training diary with information regarding the frequency of exercises, the presence of symptoms during the exercise, the perceived exertion, and the number of daily steps.

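### The stated costing rule does not reach the devices given to the home arm, and covers its phone calls only if the hospital table prices them, so the home programme's cost would be understated by an unknown amount

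*Protocol article*

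**What the plan says.** The Protocol article's section on secondary outcomes sets the costing method in one sentence. Programme cost is obtained by "calculating the total sum of each procedure in the 2 groups". For prices, that sentence points to the hospital's "payments table for procedures and services". The section fixes the time point as well: "The cost analysis and morbidity variables will be evaluated after 3 months and after 3 and 6 months, respectively, in both groups". No other price source appears in the article.

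The two arms use different resources. Under *Traditional and Face-to-Face Cardiac Rehabilitation as Control Group*, control has 24 supervised and 36 home sessions, with a training diary. Under *Home-Based Cardiac Rehabilitation*, the home arm has 2 supervised and 58 home sessions. That section adds telephone contact ("Weekly phone calls will be programmed to check the correct execution of the previous stage of the program"), a device for each person ("A heart rate monitor with the heart rate zone individually calculated will be given to each participant at the first supervised session"), a pedometer for each person, and first-week training in the equipment. The control description mentions neither devices nor calls.

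The abstract's conclusions describe the home protocol as one that "uses an accessible and low-cost technology".

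**The concern.** The rule names what is counted (procedures) and one source of prices (a hospital payments table). That suits control's distinctive resource, the supervised session at the centre. It does not suit the home arm's distinctive resources. A monitor or pedometer bought for a participant is an item of equipment, neither a procedure nor a service. A weekly call might count as a service, but only if the table has an entry for it.

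Among the programme resources described, whatever the rule misses here sits in the home arm alone, so on these items the error runs one way, in favour of the new programme. Cost is a named secondary outcome, and the technology is presented as low-cost. A cost comparison that does not clearly count that technology cannot show whether it is.

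**Working it through.** **The plan's own figure.** The article states no cost, unit price or expected saving, so there is none to reproduce. The check is a count of resources followed by a sensitivity calculation.

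**Inputs.**

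| Per participant | Control | Home-based | Does the stated rule reach it? |
|---|---|---|---|
| Supervised sessions | 24 | 2 | Yes, taken as procedures or services in the table |
| Educational meetings | 6 | 6 | Same number in both arms |
| Heart rate monitor | none listed | 1 | No: neither procedure nor service |
| Pedometer | none listed | 1 | No: neither procedure nor service |
| Weekly calls over 12 weeks | none listed | about 12 | Only if the table prices them as a service |
| Device training, first week | none listed | yes | Yes, if given inside a supervised session; otherwise unclear |

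Session counts, devices and calls come from the two group descriptions; the educational meetings come from the *Intervention* section.

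**Totals at the planned 36 per arm** (from *Sample Size*, used here only to scale up):

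- Supervised sessions: control 36 × 24 = 864; home 36 × 2 = 72.
- Calls, home arm: 36 × 12 = about 432.
- Devices, home arm: 36 monitors + 36 pedometers = 72.

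**Effect on the comparison.** Assume that every supervised session carries the same tariff and that the educational meetings cost the same in both arms. Let x be the value of the omitted home-arm items per participant, in session tariffs.

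- Apparent saving per home participant: 24 - 2 = 22 sessions.
- True saving: 22 - x sessions.
- Home/control cost ratio on supervised sessions alone: apparent 2/24 = 0.08; true (2 + x)/24.

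The article gives nothing from which to choose x. The values below are assumptions that show the range:

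| x (assumed) | True saving, sessions | Apparent ÷ true saving | True home/control ratio |
|---|---|---|---|
| 0 | 22 | 1.00 | 0.08 |
| 1 | 21 | 22/21 = 1.05 | 3/24 = 0.13 |
| 2 | 20 | 22/20 = 1.10 | 4/24 = 0.17 |
| 5 | 17 | 22/17 = 1.29 | 7/24 = 0.29 |
| 10 | 12 | 22/12 = 1.83 | 12/24 = 0.50 |
| 22 | 0 | not defined | 24/24 = 1.00 |

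If the 6 educational meetings are also priced at one tariff each in both arms, the ratio becomes (8 + x)/30: 0.27 at x = 0, 0.43 at x = 5, 0.60 at x = 10 and 1.00 at x = 22. The saving in sessions and the break-even point do not change.

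**The case against.** The strongest reply is that the text does not exclude anything. It does not say that procedures alone will be counted; the table covers services too, which could include calls and training; and considering a table is not a promise to use no other price. The table itself is not shown. Device training may take place in the supervised sessions, since the monitor is handed over at the first of them, and those sessions would be priced. All of this stands. A reader might infer that devices, training and calls are all valued at zero; the article does not support that. The gap is clear for the devices and conditional for calls and training.

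A reader might also infer that the saving is overstated severalfold, or that the low-cost description is a product of the costing rule. Neither is supported. No prices are given, so any large value of x is a guess; x = 1 would overstate the saving by only about 5%. The low-cost phrase describes the technology chosen for the programme and is not a result of the cost analysis.

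Two further points have weight. A tariff basis can miss costs in either arm: the introduction names transport as a barrier, and control attends more often. Any correction should therefore apply one resource list to both arms. Also, a journal article may leave costing detail to a fuller document. That would excuse silence, but here the article states a rule, and the rule as stated does not reach the devices.

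**Conclusion.** The point holds in a limited form. Followed as written, the costing rule prices the 22-session difference in supervised sessions but leaves out at least the monitor and pedometer supplied to each home participant, and leaves out about 12 calls each unless the table lists them as a service. The home programme's cost would then be understated and its saving overstated.

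The size is unknown. The true saving is 22 - x sessions per participant, so the home arm stays cheaper unless the omitted items are worth 22 session tariffs or more. This rests on one tariff for all supervised sessions, equal cost of the educational meetings in both arms, and programme costs only, without patient costs such as travel. The primary outcome is not affected. The change is worth making because cost is a named outcome and the omission bears on one arm only.

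**What to change.** Define programme cost as the payments-table items plus:

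- the cost of the monitor and pedometer per participant, spread over users if units are reused;
- staff time for the telephone calls, unless the table already prices them as a service;
- staff time for device training, where it is not already inside a priced supervised session.

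Write one list of resource items with a price source for each, apply it to both arms, and report the arm difference with and without the added items.

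The cost is a little extra costing work: device prices and a record or estimate of staff time per call. No new patient data and no change to the design are needed. The downside for the sponsor is that the home programme's saving may look smaller.

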**Primary outcome**								
	Compliance on cardiac rehabilitation sessions		—^a^	X^b^	—	—	X	—
**Secondary outcomes**								
	Functional capacity		X	X	X	X	X	X
	Cost analysis		—	X	—	—	X	—
	Morbidity		—	X	X	—	X	X
	**Risk factors**							
		Resting blood pressure	X	X	X	X	X	X
		Waist circumference	X	X	X	X	X	X
		Fasting glucose	X	X	X	X	X	X
		Glycohemoglobin	X	X	X	X	X	X
		Total cholesterol	X	X	X	X	X	X
	**Heart health behaviors**							
		Quality of life	X	X	X	X	X	X
		Depression	X	X	X	X	X	X
		Physical activity level	X	X	X	X	X	X
		Knowledge	X	X	X	X	X	X
	Usability		—	—	—	—	X	—

^a^No collection for the specified outcome measure on that date.

^b^Collection for the specified outcome measure on that date.

### Data Monitoring

An independent researcher, who will be blinded to the group allocation, will perform database management and the statistical analysis.

### Sample Size

On the basis of previous CR studies [34] and on our 7-year experience in providing rehabilitation services in a university hospital, we estimated a compliance of 70% in the control group and of 96% in the home-based group. We calculated that for an alpha significance level of 5% and a power of 80% in the Fisher exact *t* test, the sample size of each group should be at least 36 volunteers. We also calculated the sample size for the secondary outcome, the functional capacity (ISWT), considering an arbitrary small size effect of 0.25. To detect a statistically significant difference within and between groups (2×2), at least 34 volunteers in each group are needed, keeping the same values of alpha and power. After a pilot study with 10 subjects in each group, the sample calculation will be performed again. All the calculations were made using the G Power 3.1.9.2. software (Franz, Universitat Kiel) [35].

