## Methods

### Study Design and Procedure

The study is a single-blind, randomized controlled trial. The researchers will be blinded for the treatment’s allocation during the duration of the trial. Owing to the nature of the intervention, neither the participants nor the program staff can be blinded to the allocation type. Patients will be recruited at the outpatient University Hospital's CR Center. The study will conform to the Consolidated Standards of Reporting Trials (CONSORT) guidelines for nonpharmacological interventions [20]. After being invited to participate in the study, the volunteers will sign a consent form and will be randomized into 2 different groups: traditional CR (mostly supervised) and home-based CR (mostly unsupervised). The randomization will be made in blocks of 4 volunteers at a time [21]. A blinded researcher will evaluate the participants before and after the intervention and will collect the data into a database.

This study protocol is in accordance with the most recent version of the World Medical Association Declaration of Helsinki. This study was approved by the Ethics Committee in Research of the Universidade Federal de Minas Gerais, Brazil and was registered under the CAAE 51528615.3.0000.5149, on February 23, 2016. The CONSORT flowchart is reported in Figure 1.

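### The sample size stated for the walk test (34 per group, 80% power, within and between groups) does not follow from an effect of 0.25 at any plausible correlation, and that effect is not small

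*Protocol article*

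**What the plan says.** The Sample Size section of the protocol article first sizes the trial on compliance (70% versus 96%), giving at least 36 per group. It then gives a second calculation for ISWT distance, "considering an arbitrary small size effect of 0.25". The conclusion is: "To detect a statistically significant difference within and between groups (2×2), at least 34 volunteers in each group are needed". The error rates come from the primary calculation ("alpha significance level of 5% and a power of 80" percent) by "keeping the same values of alpha and power". The software is named: "All the calculations were made using the G Power 3.1.9.2. software". The section also promises to repeat the calculation after a pilot of 10 subjects per group.

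The section does not say whether 0.25 is Cohen's f or a standardised mean difference. It gives no correlation between the two measurements, and it does not say which of the within-subject, between-group and interaction effects produced the 34. Equal allocation is implied by the equal group sizes and by Study Design and Procedure ("The randomization will be made in blocks of 4 volunteers at a time").

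**The concern.** A 2×2 repeated-measures design has several effects, and the same f leads to very different sample sizes for them. A positive correlation between visits lowers the number needed for the interaction and raises the number needed for the between-group effect. One number offered for differences both within and between groups therefore needs checking against each effect.

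If the figure is wrong, the article credits the trial with 80% power for a small between-group difference in functional capacity that it does not have. A reader weighing a non-significant ISWT result would then overrate what that result excludes.

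**Working it through.** **Inputs from the Sample Size section.** Two groups (k = 2), two measurements (m = 2), alpha 0.05, power 0.80, effect 0.25, stated n 34 per group (N = 68), planned n 36 per group (N = 72).

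**Assumptions, because the article is silent.** The effect is Cohen's f, the usual metric for a 2×2 repeated-measures analysis of variance. The correlation ρ is 0.5, with a range shown below.

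**Formulas.** Noncentral F with 1 and N − 2 degrees of freedom:

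- Interaction: λ = f²·N·m / (1 − ρ)
- Between groups: λ = f²·N·m / (1 + (m − 1)ρ)

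**Trying to reproduce 34, at ρ = 0.5**

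- Interaction, N = 34: λ = 0.0625 × 34 × 2 / 0.5 = 8.5, power 80.7%. N = 32 gives 78.1%. The requirement is 34 in total, 17 per group.
- Cross-check: at ρ = 0.5 the SD of a change equals the SD of a single measurement, since √(2 × 0.5) = 1. A two-sample t test on changes with a difference of 1.0 SD also needs 17 per group.
- Between groups, N = 98: λ = 0.0625 × 98 × 2 / 1.5 = 8.17, power 80.8%. The requirement is 98 in total, 49 per group.
- Between groups, N = 68: λ = 0.0625 × 68 × 2 / 1.5 = 5.67, power 65.0%. N = 72 gives 67.6%.
- Interaction, N = 68: λ = 17.0, power 98%.

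**Range over the correlation, f = 0.25**

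| ρ | Total N, interaction | Total N, between | Between-group power, 34 per group | Between-group power, 36 per group |
|---|---|---|---|---|
| 0 | 66 | 66 | 82% | 84% |
| 0.1 | 60 | 72 | 78% | 80% |
| 0.3 | 46 | 84 | 71% | 74% |
| 0.5 | 34 | 98 | 65% | 68% |
| 0.7 | 22 | 110 | 60% | 62% |

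For ρ of about 0.02 to 0.05 the between-group test needs exactly 68 in total, and those 68 give the interaction 83 to 84% power. Only there does 34 per group come out as the requirement for both tests. The interaction alone never needs 34 per group at ρ ≥ 0; its maximum is 33 per group, at ρ = 0.

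**Is 0.25 small?** In the 2×2 interaction, f = 0.25 places each cell mean 0.25 SD from its additive value. Each arm's change then departs by 0.5 SD in opposite directions, so the arms differ in change by 1.0 SD. As a between-group effect, means at ±0.25 SD differ by 0.5 SD. If 0.25 was instead meant as 0.25 SD between groups, a two-sample t test needs 253 per group, and 36 per group has 18% power.

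**What 36 per group can detect.** For a two-sided two-sample comparison at one follow-up visit with 80% power, the detectable difference is 0.67 SD. Adjusting for baseline multiplies this by √(1 − r²): 0.67 × √0.75 = 0.58 SD at r = 0.5, and 0.67 × √0.51 = 0.48 SD at r = 0.7. Both values of r are assumptions.

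**The case against.** The strongest defence is that the article gives no correlation, so the figure cannot be called impossible. That stands: at ρ of about 0.02 to 0.05, 34 per group serves both tests. A reader might infer that no reading yields 34 per group, or that 34 is certainly a mislabelled total. The documents support neither. The mislabelled total is an inference from the exact match at ρ = 0.5. A near-zero correlation between two walk tests in the same patient would, however, be a poor planning assumption, and the article does not claim one.

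Second, the interaction is among the effects that Statistical Analyses plans to test, and for it the stated n is conservative (98% power at ρ = 0.5). That also stands, but the power is for a 1.0 SD difference in change, and the sentence claims between-group differences as well.

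Third, a reader might infer that the trial is too small or that its total is wrong. It is not shown to be: the 72 comes from the primary outcome, and that calculation reproduces (Fisher exact power 81.3% at 36 per group, 79.6% at 35).

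Fourth, a reader might infer that the trial will report a null ISWT result as comparable effectiveness. The article uses that term only for earlier home-based studies and states no such plan.

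Finally, sizing on two of the three visits is a legitimate simplification and is not part of this point. The recalculation after the pilot is welcome, but it does not correct the printed figure.

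**Conclusion.** Wrong as written; moderate severity. With f = 0.25, 34 per group gives the between-group comparison less than 80% power at every correlation in the table from 0.1 upwards: 78% at 0.1, 65% at 0.5 and 60% at 0.7. At the planned 36 per group, power is about 80% at 0.1 and falls to 68% at 0.5 and 62% at 0.7. At an assumed 0.5 the interaction requires 34 in total, half the number printed.

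The word small and the number 34 cannot both stand: on the f scale the effect is 0.5 to 1.0 SD, and on the SD scale 253 per group would be needed. The exact sizes rest on reading 0.25 as Cohen's f and on the assumed correlation. The mismatch between the stated effect, power and n holds over the plausible range. The consequence is limited because ISWT is a secondary outcome and its calculation does not determine the sample size.

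**What to change.** In the ISWT part of Sample Size:

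- Delete the word small and the per-group 34.
- Name the effect-size metric, the assumed correlation and the effect that was powered. If that was the interaction at f = 0.25 and correlation 0.5, write 34 participants in total.
- Do not claim 80% power for the between-group difference.
- State what the design delivers, for example: with 36 per group, two-sided alpha 5% and 80% power, the detectable ISWT difference at a single follow-up visit is about 0.67 SD unadjusted; adjusted for baseline it is about 0.58 SD if the correlation with baseline is 0.5, or 0.48 SD if it is 0.7.
- Carry the corrected calculation, with the correlation stated, into the recalculation planned after the pilot.

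The cost is a reworded passage and a slightly less favourable stated figure. Neither the design nor the sample size changes.

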### Statistical Analyses

Data will be presented as a measure of the central tendency and dispersion. Data distribution will be analyzed using the Shapiro-Wilk test. All statistical analyses will be performed considering the intention-to-treat analysis and a per protocol basis to mitigate bias. The comparison between groups of the primary outcome will be made using the Fisher exact test, considering that the expected frequency of noncompliance of the home-based group may assume a value lower than 5%. Differences between groups and at the follow-up 3 and 6 months after the intervention, in addition to the interaction effect, will be analyzed using the generalized estimation equations [36]. In all models, the endpoint variable will be analyzed as a dependent variable and the variable at baseline and after 3 months as independent variables. An alpha value of 5% will be considered for statistical significance. Post hoc tests will be performed where significant differences are observed between the groups.

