**Methods:**

We present here a two-arm, single-blinded, and randomized controlled design protocol, which compares the traditional cardiac rehabilitation (CenterRehab) with the home-based cardiac rehabilitation (Home-Based) in 72 patients affected by CAD. The primary outcome is the compliance to the cardiac rehabilitation sessions. The secondary outcomes (to evaluate effectiveness) include measurable variables such as functional capacity, CAD risk factors (blood pressure, waist circumference, glycemic, cholesterol levels, depressive symptoms, and the level of physical activity), the patient’s quality of life, the disease knowledge, and the morbidity rate. Parameters such as the program cost and the usability will also be evaluated. The programs will last 12 weeks, with a total of 60 rehabilitation and 6 educational sessions. Patients of the CenterRehab program will participate in 24 supervised sessions and 36 home sessions, while the patients of the Home-Based program will participate in 2 supervised sessions and 58 home sessions, guided by telephone. After the 12-week period all participants will be recommended to continue practicing physical exercises at home or at a community center, and they will be invited for re-evaluation after 3 months. The outcomes will be evaluated at baseline, and after 3 and 6 months.

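### The stated reason for the Fisher exact test is not a criterion for it; the test is valid and adequately powered, but Boschloo's test would add about 7 points of power at 36 per arm

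*Protocol article*

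**What the plan says.** The primary outcome is binary, the "percentage of participants who completed at least 75% (45/60) of the sessions" (Primary Outcome). Sample Size gives the planning rates, "we estimated a compliance of 70% in the control group and of 96% in the home-based group", and sizes the trial "for an alpha significance level of 5% and a power of 80% in the Fisher exact" test, concluding that "the sample size of each group should be at least 36 volunteers". The abstract gives the total: "in 72 patients affected by CAD". Study Design and Procedure randomises in blocks of 4.

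Statistical Analyses uses the same test: "The comparison between groups of the primary outcome will be made using the Fisher exact test". The reason given is "considering that the expected frequency of noncompliance of the home-based group may assume a value lower than 5", where the article prints the 5 as a percentage. On the level it says "An alpha value of 5% will be considered for statistical significance".

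Results reports 51 patients consented between February 2018 and August 2019, all with a 3-month evaluation, and recruitment ending in October 2019. Data Monitoring gives database management and analysis to an independent researcher blinded to allocation.

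**The concern.** Two things are at issue.

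First, the reason does not support the choice. Whether an exact test is needed depends on how many events are expected in the cells, not on whether a rate is below 5%. At 4% noncompliance a large trial would have no need of Fisher's test.

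Second, the choice has a price. Fisher's test conditions on the total number of compliers as well as on the arm sizes. In this design the arm sizes are set by randomisation, but total compliance is not. Conditioning leaves few attainable p-values, so the real type I error lies well below the nominal 5%, and power is lost with it. An exact test that does not condition on the total can use more of the 5% and still hold it. That matters more in a trial that reports slower recruitment than estimated.

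**Working it through.** **Inputs.** Compliance 0.70 (control) and 0.96 (home-based), alpha 0.05, power 0.80 and 36 per arm, all from Sample Size; total 72 from the abstract. Sidedness is not stated; two-sided is assumed because it reproduces the article's figure.

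**1. The article's own sample size.** Power is the sum, over all pairs (x, y) with Fisher p ≤ 0.05, of Bin(x; n, 0.70) × Bin(y; n, 0.96).
- n = 35 per arm: 79.6%
- n = 36 per arm: 81.3%

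So 36 per arm reproduces exactly.

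**2. The stated reason.** Planned home-based noncompliance is 1 − 0.96 = 4%, so the sentence is true as a statement about a rate. The count rule uses the pooled rate under the null:
- pooled noncompliance = (0.30 + 0.04)/2 = 0.17
- expected noncompliers per arm = 36 × 0.17 = 6.12, above 5

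At the planned size the usual rule is not met.

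**3. Size and power at 36:36.** Size is the largest rejection probability over a common compliance rate from 0.001 to 0.999. Boschloo's test orders the tables by their Fisher p-value and sets the largest cut-off whose size stays at or below 5%. Fisher's own cut-off already satisfies that, so Boschloo rejects whenever Fisher does and can never have less power.

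| Test | Maximum size | Power, 70% v 96% |
|---|---|---|
| Fisher | 2.79% | 81.3% |
| Boschloo | 4.94% | 88.3% |
| Barnard (pooled z, exact unconditional) | 4.94% | 88.5% |
| Uncorrected chi-square | 5.78% | 89.6% |

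Boschloo gains 88.35 − 81.30 = 7.0 points. The chi-square does not hold 5% and is no alternative.

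In equal arms Boschloo reaches 80% at 33 per arm (81.6%; Fisher 75.8%) and just misses it at 32 (79.95%). Fisher needs 36.

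**4. Dependence on arm sizes** (control/home-based, same rates).

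| Split | Fisher | Boschloo | Gain (points) | Fisher maximum size |
|---|---|---|---|---|
| 36/36 | 81.3% | 88.3% | 7.0 | 2.8% |
| 35/36 | 86.7% | 88.3% | 1.6 | 3.7% |
| 36/35 | 81.9% | 84.4% | 2.5 | 3.7% |
| 37/36 | 83.4% | 85.6% | 2.1 | 3.8% |
| 36/37 | 87.9% | 89.2% | 1.4 | 3.8% |
| 26/25 | 64.4% | 68.4% | 3.9 | 3.8% |
| 25/26 | 72.6% | 75.6% | 3.0 | 3.8% |
| 28/28 | 63.5% | 75.5% | 12.0 | 2.8% |

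If blocks of 4 hold two patients per arm, 72 = 18 × 4 gives 36:36. With 51 patients, 12 full blocks give 24:24 and the remaining three split 2:1, hence 26/25 or 25/26. The 28/28 row is a projection: 51 patients over 19 months is about 2.7 a month, and 51/19 × 21 ≈ 56 by October 2019. No section states that size.

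**5. Dependence on the rates at 36:36.** Fisher v Boschloo: 75% v 96%, 63.8% v 74.9%; 70% v 92%, 58.5% v 68.7%; 60% v 90%, 80.0% v 86.4%.

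**The case against.** The strongest reply is that nothing is broken. The trial is sized for Fisher's test and analysed with it, the promised 80% is delivered at 36 per arm, and type I error is controlled. The conservatism has been paid for in the sample size. All of this stands. It limits the point to an efficiency gain.

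A second reply is that the gain is fragile. That is also right: equal arms make Fisher's p-values coarse, and one patient's difference near 36 cuts the gain from 7.0 to between 1.4 and 2.5 points. The planned split is nevertheless 36:36, so the 7-point figure is the one for the design as written.

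Third, conditioning on both margins can be defended: if treatment affects no patient's compliance, the total is the same under every allocation. That makes Fisher a legitimate choice. It does not remove the power difference.

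Fourth, the sentence on 5% may be loose wording for a count. The home-based arm's own expected count is 36 × 0.04 = 1.44, and at 28 per arm even the pooled count is 28 × 0.17 = 4.8, below 5. But a small count argues against the chi-square approximation, not for Fisher over Boschloo, since both are exact.

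A reader might infer several stronger claims:
- **A general loss of up to 12 points.** Twelve appears only at the projected 28/28 among these splits.
- **An actual size always under 3%.** It is 3.7% to 3.8% in the unequal splits above.
- **A misquoted rule.** The article cites no rule, and its statement about the rate is true on its own figures.
- **A faulty or underpowered primary analysis at 72 patients.** The reproduced 81.3% contradicts this.

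**Conclusion.** The point holds as a modest one. The justification printed for the Fisher test is not a valid reason for choosing it, and at the planned size the article's rates do not meet the usual count criterion either (6.1 against 5). The test itself is valid, consistent with the sizing and adequately powered at 36 per arm.

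What is forgone is about 7 points of power at 36:36 (81.3% against 88.3%), with the 5% level still held. This rests on two-sided testing, the planning rates of 70% and 96%, and exact balance. At the enrolment reported in the article the gain would be 3 to 4 points. Being a cheap improvement rather than a correction of an invalid analysis, it need not be made for the trial to be interpretable.

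**What to change.** Delete the clause about noncompliance below 5%. Name Boschloo's exact unconditional test, two-sided at 5%, as the primary test of compliance, with a matching exact unconditional confidence interval for the difference in proportions. Keep Fisher's test as a sensitivity analysis, which also preserves the link to the sample size calculation. If the sponsor prefers to keep Fisher as primary, correcting the justification is enough.

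The edit is about one sentence and the test is in standard software. There are two costs. Boschloo's test is less familiar to readers. The change also comes late: all 51 enrolled patients already have the 3-month evaluation at which the primary outcome is assessed, and Sample Size foresees a recalculation after a pilot of 10 per group, which may have involved looking at compliance. The amendment should therefore be dated, state what compliance data had been seen and by whom, and be documented as made before anyone sees compliance by arm. The blinded analyst described under Data Monitoring makes that feasible. If compliance by arm has already been seen, Fisher should stay primary and Boschloo be reported as supportive.
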